## Abstract

**Background:**

Chronic rhinosinusitis with nasal polyps (CRSwNP) is a chronic inflammatory condition affecting the nasal passages and paranasal sinuses. It is characterized by persistent inflammation and often leads to a considerable decline in health-related quality of life (HRQoL). A subset of these patients—approximately 17.7%—have NSAID-exacerbated respiratory disease (N-ERD), a more severe form that frequently necessitates repeated sinus surgeries and rescue therapies. Compared with individuals without N-ERD, affected patients are more prone to asthma flare-ups, severe hypersensitivity reactions, and loss of smell. Treatment with acetylsalicylic acid (ASA) following desensitization (ATAD) has been suggested as a therapeutic option in cases of severe CRSwNP with N-ERD. While this approach may offer symptom improvement, decreased polyp burden, and enhanced QoL, it is not without risks, such as gastrointestinal irritation and bleeding complications. This randomized, double-blind, placebo-controlled clinical trial (RDBCT) assesses the effectiveness and safety of ATAD in comparison with placebo in patients suffering from severe CRSwNP, N-ERD, and asthma. The study explores various outcomes, including reduction in polyp burden, improvement in QoL, treatment-related side effects, and biomarker analyses derived from nasal swabs, blood, and urine samples.

**Methods:**

AirGOs Medical is an investigator-initiated RDBCT conducted at Helsinki University Hospital. Participants are randomized to receive either ATAD or placebo. The primary endpoint is the change in the SNOT-22 score observed at the 11-month follow-up. Secondary measures include variations in nasal polyp scores, CRS symptom control, general HRQoL, work productivity loss, peak nasal inspiratory flow (PNIF) with or without acoustic rhinometry (ARM), olfactory function assessed by the Sniffin' Sticks identification test, spirometry, peak expiratory flow (PEF), and histopathological findings at the 12-month follow-up.

**Discussion:**

The AirGOs Medical trial is expected to generate data on the therapeutic value and safety profile of ATAD in patients with coexisting severe CRSwNP, N-ERD, and asthma, potentially informing future clinical practice.

**Trial registration:**

[ClinicalTrials.gov], identifier [NCT03825757]. Registered on 28.2.2019.

## Introduction

Chronic rhinosinusitis (CRS) is defined as persistent inflammation of the nasal cavity and sinuses lasting over 12 weeks, with a reported prevalence of 3%–11% (1, 2). It is divided into two subtypes: CRS with nasal polyps (CRSwNP) and without (CRSsNP). CRSwNP affects 0.5%–4.5% of the population and is associated with significant inflammation, diminished quality of life (QoL), and frequent recurrences despite therapy. The disease imposes both health and economic burdens (3, 4).

NSAID-exacerbated respiratory disease (N-ERD) is a chronic eosinophilic disorder affecting individuals with asthma and/or CRSwNP, triggered by NSAIDs such as acetylsalicylic acid (ASA). It is characterized by a triad of asthma, CRS, and NSAID intolerance, often accompanied by nasal polyps (5). Symptoms such as nasal blockage, wheezing, and dyspnea typically occur 30–180 min after NSAID use (6). N-ERD may appear before or alongside asthma or CRS (7). Among adults with asthma, prevalence is 3%–21%, increasing in severe asthma and CRSwNP cases (8). In Finland, N-ERD affects 1.4% of adults and 17.7% of CRSwNP patients (9). These patients often present with more severe upper airway symptoms, higher CT scores, and a greater risk of polyp recurrence than NSAID-tolerant CRSwNP patients (3, 6, 10).

Conventional CRSwNP treatment includes nasal saline rinses and intranasal corticosteroids. Advanced cases may require systemic corticosteroids, antibiotics, sinus surgery, or biologics (3). N-ERD treatment primarily involves NSAID avoidance and education about safe alternatives, including paracetamol and COX-2 inhibitors such as celecoxib and etoricoxib (3, 6, 7). However, avoiding NSAIDs alone does not halt disease progression (11). While low-salicylate diets have been suggested to help, clinical evidence remains limited.

ASA desensitization involves gradual exposure to ASA to induce tolerance maintained by daily dosing (3). It is typically indicated for poorly controlled CRSwNP or concurrent need for ASA due to cardiovascular comorbidities (12). The desensitization protocol takes advantage of a post-dose refractory period lasting 24–72 h, during which symptoms often improve (3, 13). The Scripps Clinic protocol—gradually escalating to 625 mg twice daily—is commonly used and conducted under medical supervision (3, 14).

ATAD with oral ASA has been shown to improve QoL and reduce polyp recurrence in N-ERD patients. It leads to better symptom control, smaller polyps, and decreased need for additional treatments, such as corticosteroids. Nonetheless, it carries side effects including gastrointestinal irritation, bleeding, and abdominal pain, which can hinder compliance (3, 15, 16). Nasal ASA, in contrast, lacks sufficient evidence for clinical efficacy and has not demonstrated benefit in this patient group (16, 17).

With the rise of safer biologics, evaluating the cost–benefit of ASA therapy remains crucial. This randomized, double-blind placebo-controlled trial (RDBCT) aims to assess the efficacy and safety of ATAD in patients with severe CRSwNP, N-ERD, and asthma. The hypothesis is that ATAD improves QoL and reduces polyp size more effectively than placebo, but with a higher risk of adverse effects. Additionally, nasal samples will be analyzed for genome-wide molecular and microbiome markers, while lipid mediators will be quantified from blood and urine using mass spectrometry and chromatography. These data will be assessed using linear mixed models.

## Materials and methods

### Permissions

The study has been approved by the Ethics Committee (AirGOs Medical, HUS/1801/2017) and National Drug Agency (CT 2017-0015070-42, KL/41/2018) and has been registered to ClinicalTrials.gov (NCT03825757).

### Subjects

The target number of participants for the study is 75 adult N-ERD patients with CRSwNP. This target was determined based on a power calculation, assuming a mean posttreatment difference of at least 13 in the sinonasal outcome test-22 (SNOT-22) between the treatment arms. In a previous study, the response within each subject group was normally distributed with a standard deviation of 17. To detect a true difference of 13 between the experimental and control means, we calculated that 42 experimental subjects and 21 control subjects would be needed to reject the null hypothesis that the population means are equal, with a power of 0.8 and a Type 1 error probability of 0.05. An estimated dropout rate of 15% was factored into this calculation, and if the dropout rate were higher, we would expect smaller effect sizes.

Had endoscopic sinus surgery been performed on 50% of the subjects prior to trial medication, the total number of participants required would have been 150. However, conducting the surgery before starting ATAD was not feasible due to the large number of subjects needed, given the limited number of N-ERD patients available for recruitment in the Hospital District of Helsinki and Uusimaa.

### Primary objective

The primary objective of this study is to assess the relative change in a validated quality of life measure, the sinonasal outcome test-22 (SNOT-22), from baseline to 11-month follow-up between the two randomized treatment arms, i.e., (i) 250 mg Primaspan tablet once daily and (ii) placebo tablet once daily, in patients diagnosed with CRSwNP and N-ERD.

### Secondary objectives

1.Assess the relative change in endoscopic nasal polyp score (NPS) between the two treatment groups at 11 months post-randomization.2.Assess the relative change in olfactory function and nasal patency measurements between the treatment groups.3.Assess the relative change in asthma-specific health-related quality of life (HRQoL), as measured by the asthma control test (ACT), among participants with asthma.4.Assess the relative change in lung function parameters and exhaled nitric oxide [fractional exhaled nitric oxide (FeNO)] between the treatment arms.5.Assess the relative change in Lund–Mackay (LM) scores on sinus CT scans between the two groups.6.Compare exacerbation rates, need for rescue treatments, work absences, overall costs, and safety outcomes between the treatment groups.7.Evaluate clinical parameters during ASA desensitization, including vital signs [ECG, forced expiratory volume in 1 s (FEV1), pulse, blood pressure], physical findings, reported symptoms, peak nasal inspiratory flow (PNIF), and adverse effects.8.Assess the frequency and nature of adverse effects associated with ATAD.9.Investigate changes in molecular markers and microbiome composition between the treatment groups.10.Identify biomarkers predictive of ATAD efficacy and safety.

### AirGOs Medical trial design

AirGOs Medical is a randomized, double-blind, placebo-controlled clinical trial. The study is investigator-initiated and was conducted at the Department of Allergology, Inflammation Center, Helsinki University Hospital. Patient recruitment began in 2019 and was completed in 2023. The trial received approval from the local research ethics boards (REBs) of all participating sites. A summary of the study design is presented in Figure 1, with each aspect of the trial described in detail below.

**Figure 1 F1:**
[figure not shown]
Flow diagram of AirGOs Medical study. CRSwNP, chronic rhinosinusitis with nasal polyps; N-ERD, NSAID-exacerbated respiratory disease; NPS, endoscopic nasal polyp score; SNOT-22, sinonasal outcome test-22; CT, computed tomography; LM, Lund–Mackay score; FeNO, exhaled nitric oxide; SpO2, oxygen saturation; nNO, nasal nitric oxide; ARM, acoustic rhinometry; FEV1, forced expiratory volume in 1 s; PEF, peak expiratory flow; PNIF, peak nasal inspiratory flow.

### Eligibility criteria

Table 1 and Table 2 show the inclusion and exclusion criteria, respectively.

**Table 1 T1:** Inclusion criteria.^a^

Uncontrolled CRSwNP, defined as high polyp grade (≥4 bilaterally)
High sinonasal outcome test-22 (SNOT-22) score (≥30)
High Lund–Mackay score of computed tomography scans or sinus cone beam tomography scans (≥14)
Previous ethmoidectomy surgery/surgeries (partial or total) for CRSwNP
A history of at least one of the following:
- >1 oral corticosteroid during the past 2 years - >3 antibiotic courses during the past 2 years This criterion is not required in patients with contraindication/adverse effects during oral steroid use

^a^
Asthma is not an inclusion criterion, although a majority has asthma.

**Table 2 T2:** Exclusion criteria.

Age <18 or >65 years
Prior or current complication of CRS (such as invasive fungal rhinosinusitis or mucocele)
Uncontrolled asthma
Negative result in ASA challenge
Immune system modifying medication or condition - Biologicals/immunosuppressive medication - Immunosuppressive disease/condition [e.g., human immunodeficiency virus (HIV), common variable immunodeficiency (CVID), specific antibody deficiency] - Immunotherapy - Daily use of systemic corticosteroids (prednisolone >10 mg or equivalent)
Use of anticoagulants, selective serotonin reuptake inhibitors (SSRIs) or beta-blockers
A multitude of diseases/conditions - Severe chronic urticaria - Gastric ulcer - Bleeding diathesis - Cystic fibrosis - Primary ciliary dyskinesia - Sarcoidosis - Granulomatosis with polyangiitis - Eosinophilic granulomatosis with polyangiitis - Other severe disease
Communication problems
Unlikely to comply
Pregnancy/breastfeeding

All patients must meet the diagnostic criteria for chronic rhinosinusitis as defined by the 2012 European Position Paper on Rhinosinusitis and Nasal Polyps (EPOS) guidelines (18). Continuous treatment with fluticasone propionate nasal drops and nasal irrigation is required for a minimum of 3 months prior to the first study visit and must be maintained throughout the trial. This treatment regimen is documented at each study visit. If an alternative treatment (e.g., intranasal corticosteroid spray) is used, the reason for its use must also be recorded at every visit.

Patients who are excluded from the study will have the reason for exclusion documented. To reduce selection bias, each study center will systematically screen all CRSwNP patients and record all screening failures. Eligible patients will receive both oral and written information about the study. For those who decline participation, age and gender data will be collected to evaluate the generalizability of the study population.

### Randomization

Patients who meet the eligibility criteria are randomized into two treatment arms in a 2:1 (ASA–placebo) ratio. The active (ASA) and placebo tablets were manufactured by Galena Pharma (Kuopio, Finland), a certified pharmaceutical company specializing in clinical trial products. Galena Pharma is responsible for both supplying the study medications and generating the randomization sequence. The tablets are packaged in sequentially numbered containers according to the randomization list.

The randomization codes are securely stored in sealed envelopes. These envelopes are only opened after the trial monitor has completed the study closure visit and has given explicit permission to open the blind.

### Follow-up

Patients are followed up at 1, 5, 11, and 12 months after randomization. A detailed overview of the follow-up procedures and assessments is presented in Figure 1.

### Definition of CRSwNP and comorbidities

The CRSwNP phenotype is defined according to the EPOS 2020 criteria, characterized by a history of nasal polyps and endoscopic evidence of nasal polyps (3). N-ERD is diagnosed based on a history of typical symptoms (wheezing, nasal obstruction, sneezing, nasal discharge, skin reactions, edema) following NSAID ingestion. Confirmation of N-ERD is made by performing an ASA challenge test in the hospital before randomization (Figure 1).

Clinical data, including history of previous polyp surgeries, time of nasal polyposis diagnosis, allergies, asthma diagnosis, occupation, work environment, smoking habits, medications, and disease history, are recorded by the investigator. Asthma diagnosis is based on a typical clinical history, physical exam, and at least one of the following physiological criteria: (i) recurrent variation of ≥20% in diurnal peak expiratory flow (PEF); (ii) ≥15% increase in PEF with β-agonist; (iii) ≥12% increase in forced expiratory volume in 1 s (FEV1) with β-agonist; (iv) ≥15% decrease in PEF or FEV1 during exercise or moderate to severe bronchial hyperresponsiveness in provocation tests. N-ERD is confirmed by a history of wheezing/cough or naso-ocular symptoms after NSAID use and/or a positive ASA challenge test. Allergy status is confirmed with a positive history and skin prick test or serum allergen-specific IgE against common aeroallergens.

### ASA desensitization before randomization

The ASA challenge and desensitization procedure is conducted for all subjects prior to randomization to confirm the N-ERD diagnosis and assess ASA tolerability. The desensitization process occurs in the daycare department and follows a modified international protocol (19). Given our retrospective data indicating poor ASA tolerability in this population (20), a prolonged desensitization protocol is used. Primaspan (Orion, Espoo, Finland) is employed for ASA desensitization.

The desensitization phase spans 4 days in a hospital setting to closely monitor responses and potential side effects. To confirm the N-ERD diagnosis, patients must demonstrate characteristic symptoms following ASA ingestion, as outlined in Table 3. Symptoms related to the airway, ENT, skin, and general symptoms, as well as FEV1, PEF, and vital signs (blood pressure, heart rate), are carefully monitored.

**Table 3 T3:** ASA challenge positive result criteria.

1	Naso-ocular alone: a 30% or > increase in at least one of the following VAS (0–10 cm) scores: nasal obstruction, nasal discharge, postnasal drip, eye itching. These may exist with or without objective signs of increased nasal turbinate swelling/discharge or eye redness in examination.
2	Naso-ocular (please see 1.) and a 15% or > decline in FEV1 or in PEF (Classic reaction)
3	Lower respiratory reaction only (FEV1 or PEF declines by >20%)
4	Laryngospasm with or without 1–3 (flat or notched inspiratory curve)
5	Systemic reaction: hives, flush, gastric pain, hypotension

On Day 1, patients receive 25 mg + 25 mg ASA, followed by 50 mg + 25 mg on Day 2, 75 mg + 25 mg on Day 3, and 100 mg + 25 mg on Day 4 (Figure 1). ASA is administered at 8 a.m. and 10 a.m. each day. Subjects may take their regular evening medication the night before but must fast from both food and medication on the morning of each ASA desensitization day. Both food and medication can be resumed after ASA administration.

## Results

### Primary and secondary outcomes

The primary outcome is the change in the SNOT-22 score at the 11-month follow-up. Secondary outcomes include changes in the endoscopic nasal polyp score (NPS), LM CT score, HRQoL, loss of productivity, nasal patency [peak nasal inspiratory flow (PNIF) ± acoustic rhinometry (ARM)], olfaction (Sniffin' Sticks identification test), lung function (spirometry, exhaled NO, and PEF), and pathological findings at the 12/24-month follow-up (Figure 1). Safety assessments, including complications and adverse effects, as well as costs and loss of productivity, will be compared between the treatment arms. Additionally, the costs of CRSwNP and asthma treatment 1 year before and 1 year after randomization will be compared by treatment arm. All outcome measurements will be conducted by trained study nurses and investigators. Physiological tests will be performed by a study nurse under the supervision of an investigator and a pulmonologist. Laboratory tests, including skin prick tests, blood tests, and tissue eosinophilia, will be conducted in accredited university hospital laboratories.

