### Lung function

Spirometry is performed at recruitment and at the cessation of medication. It is also conducted if there is suspicion of uncontrolled asthma. The minimal clinically important difference (MCID) for forced expiratory volume in 1 s (FEV_1_) in asthma is considered to be 11% (29).

Mini-spirometry (FEV_1_) is performed on the ASA desensitization days before the first dose, before the second dose, and after the second dose.

Peak expiratory flow (PEF) is measured by patients at home over one week at four timepoints: during recruitment, before ASA desensitization, at discontinuation of medication, and before the end of the trial. The MCID for PEF is an improvement of 12%, as suggested by a study on asthma patients (30).

Fractional exhaled nitric oxide (FeNO) measures airway inflammation, primarily in asthma, reflecting eosinophilic activity and disease control. The MCID for FeNO is a relative change of ≥20% (31).

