### Tissue and mucus samples

Nasal mucus, epithelial, and polyp tissue samples are collected before randomization and at 5 and 11 months after starting the IMP to examine molecular and cellular changes, as well as microbiome and transcriptome profiles related to efficacy and safety. Participants are also invited to voluntarily donate a blood sample to the Finnish National Biobank for inclusion in a nationwide genome-wide association study (GWAS) project. (https://www.finngen.fi/en).

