### Statistical methods

The primary objective of the study is to evaluate the improvement in key endpoints, including the change from baseline to 1 year after starting ATAD, in SNOT-22 scores and the endoscopic nasal polyp (NP) score. Power calculations and randomization procedures for these primary endpoints have been previously outlined. An additional secondary endpoint is the change from baseline in FEV1 at 1 year. The analysis of each imputed complete datapoint will be conducted using an analysis of covariance (ANCOVA) model, linear mixed models, incorporating baseline values, treatment group, prior surgery history, sex, age, and region as covariates. Missing data will be addressed through multiple imputation, and sensitivity analyses will be performed to assess the robustness of the results.

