Targeted biologic therapies have significantly advanced the treatment of Type 2 inflammatory diseases, including N-ERD (48). These therapies are typically considered alongside other advanced options, such as endoscopic sinus surgery and ATAD. The efficacy and safety of biologics for N-ERD patients have been demonstrated in several studies (49). Biologic therapies are recommended for patients who cannot tolerate ASA due to conditions such as gastritis, bleeding risks, or severe uncontrolled asthma (50). However, some patients may require long-term ASA or NSAIDs for other conditions, such as cardiovascular disease, making ASA desensitization a potential option for these individuals (51). To the authors' knowledge, there are no available results from RDBCT studies directly comparing ATAD with biological therapies.

Our randomized double-blind controlled clinical trial assesses the safety and efficacy of ATAD in treating patients with CRSwNP and N-ERD. We will monitor general and disease-specific HRQoL, disease control in CRS and asthma, olfactory function, endoscopic nasal polyp score, lung function, absenteeism, and decreased productivity at work, as well as treatment resource utilization. Adverse events related to the treatments will be monitored throughout the study. Participants first undergo the 4-day desensitization phase and then continue to 11-month maintenance treatment with either aspirin or placebo. Several control visits with doctors during the study will monitor adverse events, disease control, and other factors. After cessation of medication, a posttreatment visit will take place 1 month after stopping the medication. We acknowledge that the study is limited to a single hospital district, which may affect its external validity. Additionally, we recognize that the lack of a direct comparison to biological therapies limits the study's broader impact.

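### The stated timepoints of the secondary endpoints contradict each other and the visit schedule, so it is unclear whether on-treatment or post-treatment values are analysed

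*Protocol article*

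**What the plan says.** All references are to the protocol article.

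**Timepoints given to the endpoints**
- Abstract, Methods: SNOT-22 is primary at 11 months. The list of secondary measures (polyp score, nasal patency, olfaction, spirometry, PEF and others) ends with "and histopathological findings at the 12-month follow-up".
- Primary and secondary outcomes: SNOT-22 again at 11 months. A similar list of secondary outcomes ends with "pathological findings at the 12/24-month follow-up (Figure 1".
- Secondary objectives, item 1: nasal polyp score at 11 months after randomization.
- Statistical methods: SNOT-22 and polyp score are both dated one year from the start of ATAD, followed by "An additional secondary endpoint is the change from baseline in FEV1 at 1 year".

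**Visits and collection**
- Follow-up: "Patients are followed up at 1, 5, 11, and 12 months after randomization".
- Discussion: participants are desensitized over 4 days and "then continue to 11-month maintenance treatment with either aspirin or placebo". After that, "a posttreatment visit will take place 1 month after stopping the medication".
- Lung function: "Spirometry is performed at recruitment and at the cessation of medication". Otherwise spirometry is done only when uncontrolled asthma is suspected. Home PEF is recorded in four periods, including one when medication is discontinued and one before the trial ends.
- Tissue and mucus samples: "collected before randomization and at 5 and 11 months after starting the IMP".

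**The concern.** The trial has two closing visits one month apart, the first at the end of treatment and the second off treatment. The month attached to an endpoint therefore decides whether the comparison is of patients on drug or of patients who have stopped. The article gives more than one month for the same endpoint. It also names a month that is not in the schedule, and months at which the text schedules no collection of the measure.

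Trial status says that data collection is over and analysis is in progress. If the timepoints stay unreconciled, the choice between the two closing visits could be made endpoint by endpoint with data in hand. An off-treatment value also answers a different question from the 11-month primary endpoint. The plan handles missing data by multiple imputation. An FEV1 analysis tied literally to month 12 would therefore impute almost every value, and the few observed ones would come from patients with suspected uncontrolled asthma.

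**Working it through.** **The plan's own figure.** The only sized endpoint is SNOT-22. The inputs are a difference of 13, SD 17, power 0.8, type 1 error 0.05 (taken as two-sided), 2:1 allocation and 15% dropout.
- Control n = (1 + 1/2) × (1.960 + 0.842)² × (17/13)² = 20.13, rounded up to 21. Active n = 42, total 63.
- Recruited = 63 / 0.85 = 74.1, rounded up to 75.

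Both figures match the Subjects section. No sample size or power is stated for any secondary endpoint, so nothing in this point changes these numbers.

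**Treatment status at each closing visit.** Maintenance lasts 11 months, and the last visit follows one month after stopping: 11 + 1 = 12. Month 11 is the end of treatment and month 12 is off drug. This assumes that maintenance starts at or very near randomization. The 4-day desensitization before it is too short to matter.

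**Labels against schedule, from the text shown**

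| Endpoint | Labels given | Collection in the text | Conflict |
|---|---|---|---|
| Nasal polyp score | 11 months (Secondary objectives); 12 (abstract); 12/24 (outcomes section); 1 year (Statistical methods) | 11 months by the objective | Up to four labels for one endpoint |
| Pathology | 12 (abstract); 12/24 (outcomes section) | Baseline, 5 and 11 months | No scheduled sample at any stated time |
| FEV1 | 12 (abstract, as spirometry); 12/24 (outcomes section, as lung function); 1 year (Statistical methods) | Recruitment and cessation, about 11 months | No routine value at month 12 |
| PEF | 12 (abstract); 12/24 (outcomes section) | Four periods, including discontinuation and before trial end | Data at both closing times; the labels point to the off-drug one |
| SNOT-22 | 11 months (abstract, Primary objective, outcomes section); 1 year (Statistical methods) | 11 months | One section disagrees with three |
| PNIF/ARM, olfaction, general HRQoL | 12 (abstract); 12/24 (outcomes section) | Visit not given in the text; Figure 1 not shown | Could be compared off treatment |

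A 24-month assessment appears only in the outcomes section. The visit schedule ends at month 12.

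**The case against.** **The 1-year label may be loose wording.** Statistical methods uses it for SNOT-22, which three other places fix at 11 months. It may simply mean the end of treatment, when spirometry is done. This stands. A reader might infer that FEV1 cannot be analysed as planned, but the document does not support that: an end-of-treatment FEV1 is scheduled, and the heavy imputation described above arises only if 1 year means month 12. The correction is still needed, because months 11 and 12 are separate visits and the abstract sets the two labels side by side.

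**The 12/24-month label may belong to pathology alone.** It follows the last item of a long list, and the abstract's 12-month label can be read the same way. This also stands. On that reading, however, the label sits on the one measure for which the text schedules no sample at either time, and polyp score is still dated both 11 months and 1 year.

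**Figure 1 is not shown.** The article refers to it for procedures by visit, and it may list more than the text does. Pathological findings may also not be confined to the samples in the tissue section. So the supportable statement is that none is scheduled in the text shown. It would go too far to say that all such values will be missing. The figure cannot undo the contradictions between text sections.

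**Dilution is not shown.** A reader might infer that secondary effects will be diluted and attach a loss of power. That needs month 12 to be the visit analysed and the effect to fade within a month. The only related figure is a 24–72 h refractory period after a dose, which gives no rate at which clinical benefit is lost. Any power figure would need an invented retention fraction and the SNOT-22 effect as a stand-in.

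**Not every measure is known to be taken at 11 months.** The text places collection at 11 months or at cessation only for SNOT-22, polyp score, spirometry, PEF and tissue. Moving every secondary to 11 months could discard a measure taken only at month 12.

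**Conclusion.** The inconsistency is real and should be corrected. The secondary timepoints disagree between sections, one of them (24 months) lies outside the schedule, and the 12-month visit is off drug. Taken literally, pathology has no scheduled sample at its stated times and FEV1 has no routine value at month 12. The remaining measures could be compared after treatment has stopped, which could dilute an effect by an amount the document does not allow to be computed.

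The contradictions between text sections rest on the article's own words. What is collected at each visit rests on the text without Figure 1. The SNOT-22 sample size and the 11-month date that three sections give the primary endpoint are not in doubt. Outcomes accumulated over a period, such as exacerbations over the 12 months and costs in the year after randomization, are outside this point.

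**What to change.** In the abstract, Primary and secondary outcomes, and Statistical methods, name one analysis timepoint for each secondary endpoint, checked against Figure 1:
- Use the 11-month end-of-treatment visit for nasal polyp score, FEV1 (replacing 1 year), PEF and pathology, where the text supports it. Use it also for every other efficacy secondary that Figure 1 shows to be measured then.
- In Statistical methods, change 1 year to 11 months for SNOT-22 and polyp score.
- Report 12-month values as a separate analysis labelled post-treatment. If Figure 1 shows a measure only at month 12, keep that time and give it the same label.
- Delete the 24-month label, or explain which assessment it refers to.

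The cost is a text correction, with no new data and no change in sample size. The article does not say whether the randomization codes have been opened, so the correction should be dated and should state whether it was made before unblinding.
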